## Methods/Design

### Study aims

The study aims to evaluate whether LT4 benefits patients aged over 50 years with marginally raised TSH. The null hypothesis is that SCH patients over 50 years of age have the same bone health and cardiovascular outcomes when prescribed LT4 compared to those not prescribed LT4. The alternative hypothesis is that SCH patients aged over 50 years of age have worse bone health and cardiovascular outcomes when prescribed LT4 than those who are not prescribed LT4.

The objectives of the study are:

1) To use electronic healthcare records to undertake a cohort study comparing the cardiovascular outcomes (incident diagnosis of angina, myocardial infarction, stroke, peripheral vascular disease and stent/revascularisation procedure) between patients over 50 years of age with mildly elevated TSH levels prescribed LT4 versus those not prescribed LT4.

2) To use electronic healthcare records to undertake a cohort study comparing the bone health outcomes (incident diagnosis of osteoporosis, fragility fractures) between patients over 50 years of age with mildly elevated TSH levels prescribed LT4 versus those not prescribed LT4.

3) To use electronic healthcare records to undertake a cohort study comparing all-cause mortality outcomes between patients over 50 years of age with mildly elevated TSH levels prescribed LT4 versus those not prescribed LT4.

4) To use electronic healthcare records to undertake a target trial emulation study comparing the cardiovascular outcomes (incident diagnosis of angina, myocardial infarction, stroke, peripheral vascular disease and stent/revascularisation procedure) between patients over 50 years of age with mildly elevated TSH levels prescribed LT4 versus those not prescribed LT4 [46].

5) To use electronic healthcare records to undertake a target trial emulation study comparing the bone health outcomes (incident diagnosis of osteoporosis, fragility fractures) between patients over 50 years of age with mildly elevated TSH levels prescribed LT4 versus those not prescribed LT4.

6) To use electronic healthcare records to undertake a target trial emulation study comparing all-cause mortality outcomes between patients over 50 years of age with mildly elevated TSH levels prescribed LT4 versus those not prescribed LT4.

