The current research group has completed a National Institute for Health and Care Research (NIHR) Research for Patient Benefit study (Study of Optimal Replacement of Thyroxine in ElDerly (SORTED) – a feasibility study: Ref: PB-PG-0610-22139) and has demonstrated that older people can tolerate a lower dose of LT4 and hence higher TSH levels [45]. The work done in 2016 explored the relationship between the three variables: diagnosis of hypothyroidism, TSH measurement, and LT4 treatment. A feasibility analysis at one large rural general practice in Northumberland, England, with a practice list size of 11,752 found that 465 patients had been diagnosed with hypothyroidism. The prevalence of hypothyroidism at the practice was 4%, and the highest prevalence was in the 81–90 years age category, at 9.85%. The female-to-male ratio with hypothyroidism at the practice was 4.4:1.0, such that 379 females had been diagnosed. Despite 465 patients diagnosed with hypothyroidism (Read Coded), 622 patients received treatment with LT4. This is an excess of 157 patients receiving LT4 without a diagnosis of hypothyroidism. This may represent a proportion of SCH patients that are not Read Coded as hypothyroid but are receiving treatment. It is also possible that a small proportion of these patients are hyperthyroid patients receiving block and replace treatment or patients with pituitary disorders. Alternatively, some patients may report symptoms suggestive of hypothyroidism but still have normal serum thyroid function tests and receive LT4 therapy in contravention of accepted clinical practice and guidelines. For this reason, our search strategy centres upon the TSH values recorded in the database rather than a diagnosis. Between 2003 and 2015, 215 (1.9%) patients were recorded as having an age-specific index TSH as mildly elevated, in line with the TEARS study. Of those, 39% were untreated, and 61% were treated with varying degrees of treatment length. This feasibility work concludes that 53% of the treated patients may have been over-diagnosed due to their TSH level being within the range of 4.0 mIU/L and the upper TSH limit given by the TEARS study [13].

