### Statistical analysis

The sample size calculation is based on the primary outcome of determining a difference in cardiovascular outcomes between patients receiving LT4 or not. The TRUST study of 737 patients aged 65 years and older found a cardiovascular outcome rate of 4.9% in the treatment group and 5.4% in the placebo group. Therefore, based on these outcome rates, for the cohort study, the minimum sample size required is 82,118 patients. Of this sample, 41,059 patients will be prescribed LT4 and 41,059 patients will not be prescribed LT4. A matching ratio of 1:4 (treatment: no treatment) will be used for the target trial emulation study. Therefore, the sample size required is 129,020 patients, with 25,804 patients prescribed LT4 and 103,216 patients not prescribed LT4. This sample size provides a power of 0.9 and alpha of 5%. In both studies, if missing data occurs, multiple imputation methods will be used if up to 40% of the data is missing [47]. Otherwise, pairwise deletion will be used.

In the target trial emulation study, the causal contrasts of interest will be intention-to-treat effect. Chi-square analysis will be used to compare the categorical characteristics of the participants in both studies, such that a p-value of less than 0.05 will be considered significant. Descriptive statistics will be presented. In both studies, the frequency of hypothyroidism diagnosis, smoking status, sex, ethnicity, and location will be given for each group. Survival analysis methods, including Cox proportional hazard models and Kaplan-Meier curves, will be fitted to compare the time to outcome between the groups. The hazard ratios with their 95% confidence intervals will be given.

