Confounding bias, immortal time bias, and information bias will be adjusted for both the cohort and target trial emulation studies [48]. In addition, selection bias and attrition bias will be adjusted for in the target trial emulation study. Confounding factors include sex, BMI, co-morbidities, and smoking status. The adjustment for confounding factors will be done using inverse probability weighting in the target trial emulation study [49]. In both studies, subgroup analysis will be done for each cardiovascular and bone health outcome and each age group (51–60, 61–70, 71–80, 81–90, 91 + years). A subgroup analysis including patients with a TSH level between 4 0.0 mIU/L and the upper limit of their age range in the TEARS study will be carried out. Another subgroup analysis of patients who have had a TSH level of 10 mIU/L or above or not will be conducted. Also, sensitivity analysis will be undertaken in both studies for different TSH thresholds, as the standard threshold can differ between laboratories. This study will perform a secondary analysis based on baseline fT4 levels, comparing patients with a low normal versus high normal levels (below and above median levels at baseline, respectively).

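### The only stated alternative is that LT4 is worse, but both sizes assume LT4 lowers events; and the emulation's unweighted 1:4 size is not reconciled with its weighted analysis

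*Protocol article*

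**What the plan says.** The Study aims section opens with the purpose: "The study aims to evaluate whether LT4 benefits patients aged over 50 years with marginally raised TSH". It then gives a null of equal bone and cardiovascular outcomes and one alternative, in one direction: "The alternative hypothesis is that SCH patients aged over 50 years of age have worse bone health and cardiovascular outcomes when prescribed LT4" than when they are not.

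The Statistical analysis section takes its planning rates from an earlier randomised trial, which "found a cardiovascular outcome rate of 4.9% in the treatment group and 5.4% in the placebo group". From these, "for the cohort study, the minimum sample size required is 82,118 patients", split equally. For the second study, "A matching ratio of 1:4 (treatment: no treatment) will be used for the target trial emulation study", giving 129,020 patients (25,804 with LT4 and 103,216 without). On error rates it says "This sample size provides a power of 0.9 and alpha of 5" per cent. It does not say whether the test is one-sided or two-sided.

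Later in the same section, the method for confounding in the emulation is named: "The adjustment for confounding factors will be done using inverse probability weighting in the target trial emulation study". The outcome comparison in both studies is by Cox models and Kaplan-Meier curves, with hazard ratios and 95% confidence intervals.

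**The concern.** There are two mismatches.

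First, the aim asks about benefit, the alternative allows only harm, and the power calculation assumes benefit. If the planning rates were true, the study would very probably reject its null in a direction that its hypotheses do not cover. The Discussion expects the results to bear on prescribing, so an effect in either direction matters. The status of a protective result should be settled before the data are seen.

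Second, the emulation's size comes from a formula for comparing two unweighted proportions at a fixed 1:4 ratio. The analysis named for that study is weighted. Weights that vary between patients usually reduce the effective sample size, so the stated power of 0.9 describes a different comparison from the planned one, with no allowance for the change.

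**Working it through.** **Inputs.** From the Statistical analysis section: event proportion 0.049 with LT4 (p1) and 0.054 without (p2), power 0.90, alpha 5%, and k untreated patients per treated patient, with k = 1 or 4. Normal quantiles: 1.960 (two-sided 5%), 1.645 (one-sided 5%), 1.2816 (90% power).

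**Formula.** With pooled proportion p̄ = (p1 + k·p2)/(1 + k), the number treated is

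n1 = {z_α·√[(1 + 1/k)·p̄(1 − p̄)] + z_β·√[p1(1 − p1) + p2(1 − p2)/k]}² / (p1 − p2)²

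**Step 1: reproduce the stated sizes (two-sided, LT4 lower).**
- k = 1: p̄ = 0.0515; n1 = (0.61261 + 0.40054)²/0.005² = 41,059.04. The plan has 41,059 per group, 82,118 in total.
- k = 4: p̄ = 0.053; n1 = (0.49093 + 0.31226)²/0.005² = 25,804.5. The plan has 25,804 treated, 129,020 in total.

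Both match.

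**Step 2: which direction and how many sides?**
- One-sided 5% gives 33,465 per group (66,930 in total) at 1:1 and 20,983 treated (104,915 in total) at 1:4. Neither matches, so the calculation is two-sided.
- At 1:1 the formula is symmetric and cannot show direction. At 1:4 it can. With LT4 as the higher-rate group (0.054 v 0.049), p̄ = 0.050 and n1 = 25,509, not 25,804. The plan therefore entered LT4 as the group with fewer events.

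**Step 3: what the planning effect means for the stated alternative.** If the true rates are 4.9% with LT4 and 5.4% without, the 1:1 test statistic has standard error 0.0015425 under the null and 0.0015424 under these rates. The chance of a significant result in the stated direction (LT4 worse) is 1 − Φ[(1.960 × 0.0015425 + 0.005)/0.0015424], about 1 in 10 million. Almost all of the 90% power is for a result that the alternative excludes.

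**Step 4: power of the stated sizes for harm.** Power = Φ[(|p1 − p2| − 1.960·SE0)/SE1], where SE0 is the pooled and SE1 the unpooled standard error. With the rates reversed (LT4 5.4%, no LT4 4.9%):
- 1:1, 41,059 per group: Φ(1.2815) = 90.0%.
- 1:4, 25,804 treated: SE0 = 0.0015169, SE1 = 0.0015592; Φ(1.300) = 90.3%.

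The same sizes therefore serve a two-sided hypothesis.

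**Step 5: effect of weighting on the emulation.** The documents give no variance inflation for the weights, so the factors below are assumptions. Dividing 25,804 treated (and 103,216 untreated) by the factor and recomputing power at 4.9% v 5.4%:

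| Assumed variance inflation | Power at the stated 129,020 |
|---|---|
| 1.0 (as planned) | 90.0% |
| 1.2 | 84.0% |
| 1.5 | 75.1% |
| 2.0 | 62.4% |

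**The case against.** **On direction.** A directional research hypothesis tested two-sided is common and conservative. The null is equality, and hazard ratios with 95% confidence intervals are promised, so a ratio below 1 would be reported. That stands, and it means the sizes need not change. It does not remove the mismatch: the article never says the test is two-sided, and neither stated hypothesis covers the effect it was powered for.

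A reader might infer that the study is underpowered for harm. The documents do not support this. Step 4 shows about 90% for the reversed rates. A lower figure arises only by choosing another harm effect. With the untreated rate kept at 5.4%, an assumed 5.9% with LT4 gives 87.3% (1:1) and 87.7% (1:4), but an assumed 5.95%, which mirrors the ratio 5.4/4.9, gives 92.7% and 92.9%. The documents state neither rate.

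**On matching and weighting.** The two can be combined, and a condensed article may leave the mechanics to a fuller document. Weighting by an estimated propensity score does not always raise the variance either. All of that stands, so this is an unreconciled description and not a proven error. But the article itself fixes both the ratio and the adjustment method, and ties a power figure to only one of them.

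A reader might also infer from the feasibility work, where "Of those, 39% were untreated, and 61% were treated with varying degrees of treatment length", that 1:4 is unattainable or would discard most treated patients. That does not follow. The split describes 215 patients at one practice, treated at some time over 2003 to 2015, not patients starting LT4 at an emulated baseline. A matching ratio need not equal the natural share. Even at 39% untreated, the crude count of 530,792 patients with raised TSH would hold about 207,009 untreated (0.39 × 530,792), against 103,216 needed. How many remain after the age and disease exclusions is not given, so no shortfall is shown.

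**Conclusion.** The point holds in two parts.

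The stated alternative (harm only), the stated aim (benefit) and the planning effect (LT4 lower, two-sided) do not agree, and a protective finding has no prespecified inferential status. This rests on the documents' own words and on sizes that reproduce. It is a fault in the hypothesis and not in the sample size.

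The emulation's 0.9 applies to an unweighted 1:4 comparison, and the article does not connect that to the weighting it prescribes. How far the power differs is unknown. About 84% to 62% is an illustration under assumed inflations of 1.2 to 2.0, not an estimate. Whether to keep 1:4 matching is a design choice that this point does not decide.

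**What to change.** - In Study aims, reword the alternative so that bone and cardiovascular outcomes differ between patients prescribed and not prescribed LT4.
- In Statistical analysis, state that the 5% test is two-sided, and that the sizes give about 90% power for a difference between 4.9% and 5.4% in either direction (with LT4 worse, 90.0% at 1:1 and 90.3% at 1:4).
- Reconcile the matching and weighting statements: say whether the emulation is matched, weighted or both. Restate its power, or the detectable hazard ratio, for that analysis with a stated variance inflation. The table above can serve until the weights are known.

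The cost is a few sentences and one restated figure. The emulation's stated power may come out somewhat lower than 0.9. No new patients or data are needed.

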### Study design

A retrospective cohort study and a target trial emulation study will be conducted using electronic health records held in The Health Improvement Network (THIN) database.

### Study setting

THIN captures clinical data from general practices across the UK, holding anonymised records of approximately 6% of the UK population from 850 general practices. THIN has over 25 years of data recorded. To ensure a complete and reliable dataset, this project will capture data between January 1st, 2006, and December 31st, 2021. Preliminary counts from THIN show 530,792 patients with a TSH greater than 4 mIU/L. Preliminary counts also show 258,868 patients diagnosed with hypothyroidism within the same period. The variables that will be captured from the THIN database are as follows:

sex,diagnosed with hypothyroidism,date of diagnosis of hypothyroidism,date LT4 treatment commenced,first and last recorded LT4 dose,co-morbidities (heart disease, asthma, chronic obstructive pulmonary disease, diabetes, chronic kidney disease, rheumatoid arthritis, depression, dementia, dyslipidaemia, osteoporosis, fragility fractures).date of diagnosis of co-morbidities,current and past medications,date of death (if applicable),TSH, fT4, thyroxine (T4), triiodothyronine (T3), and free triiodothyronine (fT3) levels,date of recorded TSH, fT4, T4, T3, and fT3 levels,thyroid peroxidase antibody status,body mass index (BMI) at entry and end of the study period,blood pressure,smoking status.

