#### Inclusion criteria

Patients registered on the THIN database and aged over 50 on January 1st, 2006.Patients with a recording of TSH above 4.0 mIU/L between January 1st, 2006, and December 31st, 2021.Patients who are prescribed LT4 or receive no hormone replacement therapy. In the cohort study, patients in the treatment group will be prescribed LT4 before the end of the study period, December 31st, 2021. In the emulated target trial study, patients will initiate LT4 treatment and remain on it during a 5-year follow-up between January 1st, 2006, and December 31st, 2021. Patients in the emulated target trial study will be randomly assigned a strategy at baseline and be aware of their assignment.In the cohort study, patient follow-up ends at death, withdrawal from the database or December 31st, 2021, whichever occurs first.

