#### Exclusion criteria

Patients aged 50 years or under on January 1st, 2006.Patients without a recording of TSH above 4.0 mIU/L between January 1st, 2006, and December 31st, 2021.Patients diagnosed with thyroid cancer, pituitary disease or hyperthyroidism.Patients prescribed medications such as amiodarone or lithium that can affect thyroid function.Patients who have undergone thyroid surgery or radioiodine treatment, suggesting previous thyroid dysfunction.Patients receiving a different form of thyroid replacement therapy to LT4, e.g. liothyronine or combination therapy with liothyronine and LT4.Patients with a baseline diagnosis of angina, myocardial infarction, peripheral vascular disease or stroke, where cardiovascular is the outcome variable.Patients with a baseline diagnosis of osteoporosis or fracture, where bone health is the outcome variable.

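### Data capture and eligibility both open on 1 January 2006, so disease and levothyroxine use recorded only before then may be missed at baseline and old disease later counted as incident

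*Protocol article*

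**What the plan says.** In the protocol article, Study setting, the source database is described as long: "THIN has over 25 years of data recorded". The next sentence restricts what the project takes from it: "To ensure a complete and reliable dataset, this project will capture data between January 1st, 2006, and December 31st, 2021". The Methods paragraph of the Abstract gives the same span of years for the records used.

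The Inclusion criteria use the same two dates for eligibility: "Patients with a recording of TSH above 4.0 mIU/L between January 1st, 2006, and December 31st, 2021". They also ask for "Patients registered on the THIN database and aged over 50 on January 1st, 2006".

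The Study aims define the cardiovascular and bone outcomes as incident diagnoses. The Exclusion criteria remove prevalent cases, for example "Patients with a baseline diagnosis of angina, myocardial infarction, peripheral vascular disease or stroke, where cardiovascular is the outcome variable", with a parallel rule for osteoporosis or fracture. They also remove patients with certain thyroid and pituitary conditions and those who have had thyroid surgery or radioiodine.

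The variable list in Study setting includes "date of diagnosis of co-morbidities" and "current and past medications", and the date on which levothyroxine began. It does not say how far back any of these reach.

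**The concern.** A baseline exclusion can only work on records that precede the index date. If capture starts on the day the first patient can qualify, a patient whose raised TSH falls in February 2006 has about one month of captured history. A myocardial infarction coded in 2003 would then not be seen. The patient would enter as free of cardiovascular disease, and the next coded angina or infarction would count as an incident event. The same applies to osteoporosis or fracture coded before 2006, and to earlier thyroid disease, surgery or radioiodine.

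The emulation also depends on levothyroxine being initiated in the study. Without earlier prescriptions, a continuing user in early 2006 cannot be told from a new one.

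The planned contrast is small, 4.9% against 5.4%, so modest contamination of the incident outcome matters. History missing from the extract is also missing from the co-morbidity confounders, so weighting or regression on those variables would not restore it.

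**Working it through.** **Step 1: the dates side by side.**

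| Item | Section | Start |
|---|---|---|
| Data capture | Study setting | 1 January 2006 |
| Qualifying TSH | Inclusion criteria | 1 January 2006 |
| Records held in the database | Study setting | over 25 years of data |
| Look-back for baseline disease | Exclusion criteria | not stated |

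The first two coincide, and the third shows that earlier records exist. Captured history before index is therefore the time from 1 January 2006 to the index date. It is shortest for patients indexed in the early years. If index dates were spread evenly over the 16 years (an assumption), 1/16 = 6% of patients would have under one year of it, 2/16 = 12.5% under two years and 5/16 = 31% under five.

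**Step 2: can the variable list rescue it?** The co-morbidity list names heart disease, osteoporosis and fragility fractures, with diagnosis dates. It does not name stroke or peripheral vascular disease, which are both baseline exclusions and components of the primary outcome. Nothing says that dates before 2006 are kept.

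**Step 3: reproduce the planned sample size.** Inputs from Statistical analysis: p1 = 0.049, p2 = 0.054, alpha 5% (two-sided), power 0.9. With the pooled-variance formula and p̄ = 0.0515:

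n = [1.960·√(2·0.0515·0.9485) + 1.282·√(0.049·0.951 + 0.054·0.946)]² / 0.005² = 41,060 per group

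The plan states 41,059. At 1:4 the same method gives 25,805 in the treated group, against 25,804 stated. The sample size calculation is not in error.

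**Step 4: illustrate the effect of missed history.** The documents give no inputs for this, so all of them are assumptions. Let q be the share of analysed patients with missed prior disease, and r the share of those re-recorded during follow-up. The observed risk in each group is

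p* = (1 − q)·p + q·r

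Example with q = 1%, r = 0.5, equal in both groups:
- treated: 0.99 × 0.049 + 0.005 = 0.0535
- untreated: 0.99 × 0.054 + 0.005 = 0.0585
- risk ratio 0.915, against 0.049/0.054 = 0.907 planned

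| q (r = 0.5, both groups) | Risk ratio | Power at 41,059 per group | False share of untreated-group events |
|---|---|---|---|
| 0 | 0.907 | 0.90 | 0% |
| 1% | 0.915 | 0.87 | 9% |
| 2% | 0.922 | 0.84 | 16% |
| 5% | 0.938 | 0.74 | 33% |
| 10% | 0.954 | 0.59 | 51% |

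Varying r from 0.25 to 1 gives risk ratios of 0.912 to 0.922 at q = 1% and 0.939 to 0.970 at q = 10%. Power runs from 0.88 to 0.84 and from 0.71 to 0.45 respectively.

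If q differs between groups, with r = 0.5:
- 3% treated, 2% untreated: 0.0625/0.0629 = 0.994
- 2% treated, 3% untreated: 0.0580/0.0674 = 0.861

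These are risk ratios on the planning proportions. The Cox hazard ratio should move in the same directions, but its size would depend on the timing of re-recording.

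**The case against.** The strongest reply is that the 2006 to 2021 window describes the study period and is not a cut on historical codes. The Inclusion criteria call 31 December 2021 the end of the study period. Diagnosis dates, past medications and the levothyroxine start date are listed without a date limit. Exclusions for earlier thyroid surgery or radioiodine presuppose that earlier history is visible. This stands in part. A reader might infer that pre-2006 disease will certainly be missed, and the text does not establish that. What remains is that the article states a capture start and nowhere says that earlier dates are kept.

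A second reply is that a condensed article may leave the look-back length and minimum registration to the full protocol. That is accepted: their absence alone is not the point. The point is the stated capture start, equal to the eligibility start.

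Three stronger inferences also fail:
- Patients who joined a practice late might seem exposed throughout the period. The first inclusion criterion can be read as requiring registration on 1 January 2006, which would make late joiners ineligible.
- Early-indexed patients might seem to carry the longest follow-up in both studies. The emulation has a 5-year follow-up, so this fits only the cohort study.
- A definite share of false events might be put forward. Every input to such a figure would come from outside the documents.

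Equal contamination in both groups dilutes the contrast. Bias beyond that needs a difference between groups, which is plausible if known heart disease influences prescribing, but the documents do not show it.

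**Conclusion.** The point holds as a stated rule that needs correcting. As written, capture and eligibility start on the same day, although the database holds earlier records. Cardiovascular, bone or thyroid history and levothyroxine use recorded only before 2006 may be missed at baseline, mainly in patients indexed early, and re-recorded disease may enter as an incident outcome.

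The size cannot be derived from the documents. Equal misclassification would pull the hazard ratio toward 1 and cost power. Unequal misclassification could move it either way. The figures in the tables rest on assumed values of q and r and show sensitivity only; they are not an estimate for this study.

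**What to change.** In Study setting, state that 1 January 2006 to 31 December 2021 bounds the index TSH, levothyroxine initiation and follow-up only. Add that all available records before the index date will be extracted and used for the Exclusion criteria, the baseline confounders and prior levothyroxine use. Name stroke and peripheral vascular disease among the conditions captured. If earlier records are already intended, one sentence saying so is enough.

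The cost is wording and a wider data request. Some patients with old disease will now be excluded, which is the purpose. The preliminary count of 530,792 with TSH above 4 mIU/L leaves room against the 82,118 and 129,020 required, though that count is not stated to be after the age limit and exclusions. The change should be made before extraction, because analysis cannot recover records that were never requested.

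A minimum registration period before the index TSH is an optional addition that would cost a small number of patients. It does not replace the look-back: twelve months' registration would not reveal a 2003 infarction. A sensitivity analysis excluding patients indexed in the first years needs no new data and can support the main result.

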**Methods:**

This project includes a retrospective cohort analysis and a target trial emulation study using electronic patient records collected between 2006 and 2021 and recorded in The Health Improvement Network database. The primary outcome of this study is to compare the cardiovascular outcomes of subclinical hypothyroid patients aged over 50 years treated with levothyroxine compared to those untreated. Secondary outcomes are bone health and all-cause mortality outcomes. Descriptive and inferential statistics will both be employed to analyse the data. Secondary analysis will explore confounding factors, including age, sex, smoking status, body mass index, co-morbidities, and levothyroxine dosage.

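### The named confounders leave out blood pressure, which is captured, and the named co-morbidities include neither hypertension nor non-thyroid cancer

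*Protocol article*

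**What the plan says.** Three places in the protocol article bear on the adjustment set.

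- **Study setting, variables captured.** Blood pressure sits between BMI and smoking: "at entry and end of the study period,blood pressure,smoking status". The diagnoses to be captured are "co-morbidities (heart disease, asthma, chronic obstructive pulmonary disease, diabetes, chronic kidney disease, rheumatoid arthritis, depression, dementia, dyslipidaemia, osteoporosis, fragility fractures", which makes eleven conditions. Medication history is also captured ("current and past medications"), with no stated role in adjustment.
- **Statistical analysis.** "Confounding factors include sex, BMI, co-morbidities, and smoking status". For the emulation, "The adjustment for confounding factors will be done using inverse probability weighting in the target trial emulation study". No method or list of terms is tied to the cohort Cox model.
- **Abstract, Methods.** "Secondary analysis will explore confounding factors, including age, sex, smoking status, body mass index, co-morbidities, and levothyroxine dosage". This adds age and dose, but not blood pressure.

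Cancer appears once in the design, under Exclusion criteria, and only for the thyroid: "Patients diagnosed with thyroid cancer, pituitary disease or hyperthyroidism". The primary outcome is cardiovascular. All-cause mortality is a secondary outcome and has an objective of its own in each of the two studies.

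**The concern.** BMI and smoking pass from the extraction list to the confounder list, but blood pressure, which stands between them, does not. It cannot enter under co-morbidities either, because hypertension is not among the eleven. Diabetes, dyslipidaemia and kidney disease are there, so the gap is specific. The primary outcome is made up of angina, infarction, stroke, peripheral vascular disease and revascularisation, for which blood pressure is a leading risk factor.

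For mortality, non-thyroid cancer is neither an exclusion nor a named co-morbidity. If prognosis influences who is started on levothyroxine, an adjustment set without cancer may leave part of that difference in the mortality hazard ratio. The Background gives some reason to think prognosis matters. It reports a recommendation to tailor dose to age, co-morbidities and life expectancy, although it concerns dose and the same section says recommendations are not always followed.

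The study is sized for a small relative effect, so modest residual confounding is not negligible, and a larger sample does not reduce it.

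**Working it through.** **1. The plan's own figures.** Inputs from Statistical analysis: event rates 4.9% (levothyroxine) and 5.4% (none), power 0.90, alpha 5%, taken as two-sided. The standard two-proportion formula without continuity correction gives:

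- 1:1: 41,060 per group (plan: 41,059).
- 1:4: 25,805 treated (plan: 25,804).

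The stated sizes reproduce to within rounding. Nothing in this point changes them.

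**2. Planned effect as a hazard ratio.** ln(1 − 0.049) / ln(1 − 0.054) = 0.905, so |ln HR| ≈ 0.0998.

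**3. Precision at the planned cohort size.** Events: 41,059 × 0.049 ≈ 2,012 and 41,059 × 0.054 ≈ 2,217. SE of ln HR ≈ √(1/2,012 + 1/2,217) ≈ 0.031. The 95% half-width is 1.96 × 0.031 ≈ 0.060, or about 6%.

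**4. Bias from omitting a binary risk factor.** Bias factor = (1 + p1(RR − 1)) / (1 + p0(RR − 1)), where p0 and p1 are its prevalences in the two groups and RR is its risk ratio for the outcome. *Assumed, not in the documents:* hypertension in 40% of one group, 3 to 10 points more in the other, RR 1.5 to 2.0.

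| RR | Excess (points) | Calculation | Bias factor | Share of planned log effect |
|---|---|---|---|---|
| 1.5 | 3 | 1.215/1.200 | 1.013 | 12% |
| 1.5 | 5 | 1.225/1.200 | 1.021 | 21% |
| 1.5 | 10 | 1.250/1.200 | 1.042 | 41% |
| 2.0 | 3 | 1.430/1.400 | 1.021 | 21% |
| 2.0 | 5 | 1.450/1.400 | 1.036 | 35% |
| 2.0 | 10 | 1.500/1.400 | 1.071 | 69% |

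The share is ln(bias factor)/0.0998; for the last row, 0.0690/0.0998 = 0.69. Five of the six cases lie inside the 6% half-width. Only the last exceeds it.

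**5. Direction.** If the other group has the excess, the factors invert: 1/1.013 = 0.987 to 1/1.071 = 0.934. The documents do not say which group has the higher blood pressure.

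**6. What the figures leave out.** They use crude imbalance. Sex, BMI, smoking, diabetes, kidney disease, dyslipidaemia and heart disease are all listed and plausibly correlated with blood pressure. Adjusting for them would remove part of the bias, so the table is nearer an upper range for these inputs. No figure is offered for cancer, because the documents give nothing on which to base one.

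**The case against.** The strongest reply is that the lists are illustrative. Both are introduced by open words (include, including). The Statistical analysis list omits even age, which the Abstract names, so silence on blood pressure is not a decision to leave it out. The extraction list is not exhaustive either: ethnicity and location are to be reported but are not on it, and the exclusions need codes for thyroid cancer, pituitary disease and thyroid surgery that it does not show. Medication history could identify treated hypertension. This is also a condensed article, and an analysis plan not shown here may hold the full covariate set.

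Most of this stands, and it rules out three stronger readings that a reader might infer:

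- *That the hazard ratios will be unadjusted for blood pressure.* No section says so, and blood pressure is in the dataset.
- *That cancer cannot be adjusted for.* Absence from a list that is demonstrably incomplete does not show this.
- *That levothyroxine would look protective because it is withheld in cancer.* No section describes such a practice. Dementia, chronic lung disease, kidney disease and heart disease are listed and capture part of poor prognosis.

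The reply does not remove the point. The article goes beyond promising adjustment for confounding: it names variables, twice, and neither list contains a leading risk factor for the primary outcome that the study already extracts. Medications are given no adjustment role. Open wording also leaves the choice of covariates to be made after the data are seen, in a study looking for a relative difference of roughly 9%.

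**Conclusion.** The point holds as a weakness of the adjustment set as named. An analysis confined to that set would leave residual confounding of the primary cardiovascular comparison by blood pressure, and possibly of all-cause mortality by cancer.

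For hypertension the size is about 1% to 7% on the hazard ratio, in either direction, against a planned hazard ratio of about 0.905. This rests on assumed prevalences, imbalances and risk ratios, and on no credit for correlated covariates. The 69% share of the planned log effect belongs to the extreme corner and should not be quoted as the expected bias. The cancer part is qualitative only.

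The change is worth making because it costs little and the study is observational, not because the plan is shown to give a wrong answer.

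**What to change.** In Statistical analysis, name baseline blood pressure (last value before baseline) and recorded hypertension as covariates in the cohort Cox model and in the emulation weight model, for the cardiovascular and mortality outcomes. State the time point explicitly, since the extraction list gives none for blood pressure and a value recorded after treatment starts could itself be affected by treatment. Add a baseline cancer code list to the co-morbidities and adjust for it in the mortality analyses of both studies. If any of these is left out on purpose, give the reason.

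Cost: blood pressure is already to be extracted, so this adds covariate terms and code lists for recorded hypertension, if not already held, and cancer. The downside is missing blood pressure, which falls under the plan's existing rule: multiple imputation up to 40% missing, pairwise deletion beyond that. The extent of missingness should therefore be checked early. The sample sizes do not change.
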